**10. SAMPLE SIZE RE-ESTIMATION**

Sample size re-estimation shall be done if the percentage of subjects who tested positive for MTBC is higher than anticipated, the target number of enrolled subjects may be increased to ensure the study is sufficiently powered for the MITT analyses set.

[figure not shown]

## **11. GENERAL STATISTICAL METHODOLOGY**

Baseline for efficacy or safety analysis is defined as the last non-missing efficacy or safety assessment before the first dose of study drug in the Double-blind Treatment Period.

In general, descriptive statistics: n, mean, standard deviation, median, minimum, and maximum, for continuous variables and number and percentage of subjects in each category for categorical variables will be provided by treatment group for all the variables.

All source data will be presented as subject data listings.

[figure not shown]

## **12. ANALYSES SETS**

### **12.1 ALL ENROLLED SUBJECTS**

For the purpose of this SAP, subjects who signed informed consent and meet eligibility criteria (except detection of mycobacterium tuberculosis complex (MTBC)), irrespective of whether they were randomized or not. Subjects for whom MTBC is detected are included in this analyses set.

### **12.2 INTENT-TO-TREAT (ITT) ANALYSES SET**

The ITT analysis set will include all subjects who were randomised, regardless of whether the subject actually received the study drug.

### **12.3 MODIFIED INTENT TO TREAT (MITT) ANALYSES SET**

All ITT subjects who received at least one dose of study drug and these subjects will be analysed as per the randomized treatment groups. Subjects with detection of MTBC (as per results of GeneXpert TB test) indicative of active pulmonary tuberculosis will be excluded from this analyses set.

### **12.4 SAFETY ANALYSES SET**

The safety analyses set will include all subjects who receive any amount of the study drug. Subjects will be analysed according to the treatment actually received.

### **12.5 EXPANDED MICROBIOLOGICAL MODIFIED INTENT-TO-TREAT (Expanded mMITT Analyses set) ANALYSES SET**

This will be identical to the mMITT (defined in the next section) except that Subjects with sole baseline Gram-negative bacterial infection with bacteria from the *Enterobacteriaceae*, *Pseudomonadaceae* or *Yersiniaceae* are not excluded.

### **12.6 MICROBIOLOGICAL MODIFIED INTENT-TO-TREAT (mMITT) ANALYSES SET**

All MITT subjects who have received at least 1 dose of study drug and have at least 1 baseline pathogen known to cause CABP against which the investigational drug has antibacterial activity, including bacterial pathogens identified by respiratory specimen culture, blood culture, and/or urinary antigen test (e.g. *S. pneumoniae*, *S. aureus*, *H. influenzae*, *H. parainfluenzae*, *M. catarrhalis*, *L. pneumophila*) or atypical bacterial serologic response (*M. pneumoniae*, *C. pneumoniae*, *L. pneumophila*) will be included in this analyses set. Subjects with sole baseline Gram-negative bacterial infection with bacteria from the *Enterobacteriaceae*, *Pseudomonadaceae* or *Yersiniaceae* will be excluded from this analyses set.

### **12.7 CLINICALLY EVALUABLE (CE) ANALYSES SET**

[figure not shown]

The CE analyses set will include all MITT subjects who follow important components of the trial. To be included in the CE analyses set, subjects must meet all of the following criteria:

- Meet key Inclusion Criteria, including the clinical disease criteria for CABP (Inclusion Criteria #3a, #3b, #3c, #3d and #3e in the protocol)
- Do not meet key Exclusion Criteria (#1 through # 6, #16 and #18 in the protocol)
- The TOC Visit occurred within a window of 11 to 21 days. Days from the date of randomisation unless the subject was deemed a clinical failure before this visit. Note that for the purpose of this SAP, the window has been widened from 11 to 19 days to 11 to 21 days in order to allow inclusion of subjects whose visit to the clinic was delayed for social reasons
- Do not receive non-study, potentially effective against the baseline pathogen(s), systemic antibacterial therapy between Day 1 and the assessment TOC
- Do not have a clinical outcome of Indeterminate at the TOC Visit
- Receive at least 80% of the intended doses of randomised study drug therapy (based on number of tablets dispensed/received)
- Receive at least 48 h of study drug therapy to be considered an evaluable clinical failure and at least 72 h of study drug therapy to be considered an evaluable clinical success
- Do not have any other significant protocol violation(s) that may confound efficacy assessments at TOC

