#### *Investigator determined Clinical Outcome at EOT (MITT, mMITT and CE Analyses Sets)*

- Clinical Cure: Alive and signs and symptoms of CABP (dyspnoea, production of purulent sputum or pleuritic chest pain) are resolved or return to premorbid conditions and cough is improved such that further antibacterial therapy is no needed and the subject otherwise cannot be declared a clinical failure.
- Clinical Failure: The signs and symptoms of CABP (dyspnoea, production of purulent sputum or pleuritic chest pain) did not resolve or return to premorbid and/or cough worsened, such that non-study antibacterial therapy must be initiated for the treatment of CABP or death occurred prior to assessment or subject received alternative anti-microbial therapy for the treatment of CABP prior to this visit.

[figure not shown]

- Indeterminate: Study data are missing for the evaluation of efficacy at the assessment visit for any reason, including loss to FU.

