### ***Investigator determined Clinical Outcome at TOC (MITT, mMITT and CE Analyses Sets)***

- Clinical Cure, Clinical Failure or Indeterminate: Definitions are as above. Failures at EOT will be carried forward to TOC.

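### The CE set excludes clinical failures who receive effective rescue antibacterials before TOC, which raises CE cure rates and pulls the CE treatment difference toward zero

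*SAP*

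**What the plan says.** In SAP Section 12.7 the CE criteria apply jointly: "subjects must meet all of the following criteria". Four of them matter here.

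- Non-study antibacterials: "Do not receive non-study, potentially effective against the baseline pathogen(s), systemic antibacterial therapy between Day 1 and the assessment TOC". No exception is written.
- TOC visit window. This one has an exception: "unless the subject was deemed a clinical failure before this visit".
- Minimum exposure: "Receive at least 48 h of study drug therapy to be considered an evaluable clinical failure", with a longer minimum for an evaluable success.
- Compliance: at least 80% of the intended doses, with no exception for failures.

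Section 18.2 defines clinical failure at EOT as non-resolution or worsening cough "such that non-study antibacterial therapy must be initiated for the treatment of CABP or death occurred prior to assessment", or that the "subject received alternative anti-microbial therapy for the treatment of CABP prior to this visit". TOC uses the same definitions, and "Failures at EOT will be carried forward to TOC".

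Table 2 in Section 19.3 applies the one TOC-defined CE set to Day 4 response and to EOT and TOC outcome. Section 26, which lists changes from the protocol, mentions no exemption for rescued failures.

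**The concern.** The treatment that marks a subject as a failure in Section 18.2 is the treatment that removes the subject from the set in Section 12.7. A subject who fails by EOT and starts effective rescue before TOC is a failure at TOC by carry-forward and is also ineligible for CE. The set is then selected partly on its own outcome: cures stay and part of the failures go.

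This does not look intended. The list exempts failures from the visit window and sets a minimum exposure for an evaluable failure, so CE is plainly meant to contain failures. The antibacterial bullet is the one that lacks the matching exemption.

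The stake is the CE comparison of cure at EOT and TOC. In a non-inferiority trial, a set that sheds failures from both arms tends to make the arms look alike, which is the direction that favours the claim.

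**Working it through.** **The plan's own figures.** The SAP gives no CE size, CE cure rate, EOT or TOC failure rate, or share of failures rescued, so there is no CE figure to reproduce. The nearest stated figures are the MITT size and enrolment in Section 9. With 81% in each arm, a margin of 0.125, one-sided 2.5% and 90% power, the simple unpooled formula gives 207 per arm, or 414. Then 414/(1 - 0.15) = 487.1, rounded up to 488. Neither figure involves CE, so neither is touched by this point.

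**Following one subject through the text.**

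1. The subject has not resolved by EOT and starts an active non-study antibacterial for CABP. Section 18.2: clinical failure at EOT.
2. Carry-forward: clinical failure at TOC.
3. Section 12.7, window bullet: exempt as a failure. Exposure bullet: evaluable if at least 48 h of study drug were taken.
4. Section 12.7, antibacterial bullet: not met. All criteria are required, so the subject is out of CE.

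**Effect on the cure rate.** Let q be the true failure rate and f the share of failures excluded, with no cures removed:

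CE cure = (1 - q) / (1 - q·f)

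Assume a true difference equal in size to the primary margin: q = 0.225 versus 0.10, so cure is 77.5% versus 90%, with the same f in both arms.

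| f | Lower-cure arm | Higher-cure arm | CE difference (points) |
|---|---|---|---|
| 0 | 77.5% | 90.0% | -12.5 |
| 0.50 | 0.775/0.8875 = 87.3% | 0.90/0.95 = 94.7% | -7.4 |
| 0.75 | 0.775/0.83125 = 93.2% | 0.90/0.925 = 97.3% | -4.1 |
| 0.90 | 0.775/0.7975 = 97.2% | 0.90/0.91 = 98.9% | -1.7 |

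**How large f might be.** The bullet refers to the baseline pathogen(s). Read literally, it reaches only failures with an identified pathogen who are rescued before the TOC assessment, so f is the product of those two shares. With assumed ranges of 0.3 to 1.0 and 0.5 to 0.9, f runs from 0.15 to 0.90. CE cure is then 91.4% to 98.9% at q = 10%, and 82.5% to 97.6% at q = 20%. At f = 0.15 the example above gives 0.775/0.96625 = 80.2% versus 0.90/0.985 = 91.4%, a difference of -11.2 points, so the distortion is small at that end.

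**Unequal f.** Shrinkage toward zero assumes a common f. If f were 0.9 in the lower-cure arm and 0.5 in the other, the table entries give 97.2% versus 94.7%, and the sign reverses.

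**The 80% criterion.** If the intended doses are those of the full 7-day blinded course, 80% is 5.6, so 6 doses. A failure stopping at 48 to 72 h has about 2 to 3 of 7 doses (29% to 43%) and would be excluded, which would empty the 48-hour rule. Section 17, however, counts expected doses only from first to last dose and assumes a full 48 h for shorter exposure. On that basis an early-stopping failure who took every dose is about 100% compliant. Section 12.7 does not say which basis applies.

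**The case against.** A reader might infer that nearly all failures leave the set and that CE cure approaches 100% in both arms. The documents do not support that. It needs f of about 0.9 or more, and the SAP gives no rescue share. Several kinds of failure can remain: those first declared at TOC whose rescue starts at or after that assessment, deaths without effective rescue, failures given rescue that is not effective against the pathogen and, read literally, failures with no identified pathogen.

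A reader might also infer that the trial's main conclusion is at risk. It is not. The decision rule in Section 19.1 uses Day 4 response in MITT only. EOT and TOC outcomes are also analysed in MITT and mMITT, where rescued failures stay. Section 13 reports reasons for exclusion from each set by treatment, so an imbalance would be visible. The SAP nowhere calls CE the main support for the non-inferiority claim.

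It can further be argued that the bullet targets prohibited antibacterials, not foreseen rescue. Section 14 says that the CE criteria are a subset of the listed deviations, and the matching deviation carries a short label about prohibited antimicrobials. The schedule notes in Section 8 expect some failures to need alternative treatment. This makes the intent plausible but does not repair the text. That deviation has no failure exemption either, and it has no baseline-pathogen condition. Through the CE bullet on other significant violations it could therefore also remove rescued failures with no identified pathogen.

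Finally, Day 4 response is symptom-based and rescue is not part of its definition, so the cure-rate figures do not carry over to CE at Day 4.

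**Conclusion.** The point holds in a limited form. As written, Section 12.7 removes failures who were effectively rescued before TOC, which conflicts with the list's own provision for evaluable failures. CE cure at EOT and TOC is inflated in both arms and, with a common f, any true difference shrinks: from an assumed -12.5 points to -7.4, -4.1 or -1.7 at f of 0.5, 0.75 or 0.9. The failure rates and f are assumptions. Only the direction follows from the text, and only if f is similar across arms.

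The conflict between the 80% criterion and the 48-hour rule is conditional: it arises if intended doses means the full course and eases under Section 17. Using the TOC-defined set at Day 4 and EOT conditions those results on later events. That is a fair criticism but a lesser one.

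Severity is moderate: secondary analyses only, with the primary MITT analysis and the sample size unaffected.

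**What to change.** Make these changes before unblinding and record them in Section 26.

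1. Amend the antibacterial bullet in Section 12.7 so that subjects given non-study antibacterials for CABP because they are clinical failures stay in CE and count as failures. State how this bullet, and the bullet on other significant violations, applies when no baseline pathogen was identified.
2. Reconcile the 80% bullet with the 48-hour evaluable-failure rule and with Section 17. Say what intended doses means, so that the compliance criterion does not remove failures who stop early.
3. Optionally, for the CE analyses at Day 4 and EOT, use only criteria observable up to that visit.

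The cost is SAP wording and derivation code; no new data are needed. The timing matters, because deciding after unblinding which failures count would be open to the charge of being driven by the results.

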## **6. SUMMARY OF THE STUDY DESIGN**

This is a Phase III, prospective, multicentre, randomised, double-blind, comparative efficacy and safety study of oral nafithromycin versus oral moxifloxacin for the treatment of male and female adults with CABP. Subjects providing informed consent and meeting all study eligibility criteria will be enrolled in the study and randomised in a 1:1 ratio to either of the following 2 treatment arms:

- Nafithromycin 800 mg (two 400-mg tablets) orally (PO) every 24 hours (q24h) for 3 days; subjects will receive matching placebo PO q24h on Day 4 through EOT (2 tablets) and matching moxifloxacin placebo PO q24h, on Day 1 through EOT (1 capsule), to maintain the blind (2 tablets and 1 capsule in total).
- Moxifloxacin 400 mg (1 capsule: Over-encapsulated tablet) PO q24h for 7 days; subjects will receive matching nafithromycin placebo PO q24h on Day 1 through EOT (2 tablets), to maintain the blind (2 tablets and 1 capsule in total).

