## Statistical Analysis Plan (SAP) for Protocol W-4873-301

[figure not shown]

vPrior medications that have been administered within 14 days before the date of signing the informed consent or during the Screening Phase will be recorded in the electronic Case Report Form (eCRF). All medications administered after the first dose of the study drug must be recorded in the eCRF.

wBest possible efforts should be made to conduct an in-person visit. In the event that an in-person visit is not possible due to any reason, assessment may be conducted through a telephone contact.

[figure not shown]**9. SAMPLE SIZE**

This study is designed to demonstrate non-inferiority of oral nafithromycin (800 mg once daily) compared with oral moxifloxacin (400 mg once daily).

Nafithromycin will be declared non-inferior to moxifloxacin if the lower limit of the 2-sided 95% confidence interval (CI) for the difference between treatment groups (nafithromycin minus moxifloxacin) in the proportion of subjects with a favourable clinical response at Day 4 in the MITT analyses set is greater than -0.125.

In these comparisons, the margin of 12.5% has been determined based on historic data regarding the treatment effect of antibiotics.

For the determination of the study sample size, favourable clinical response rates at Day 4, obtained from studies of subjects with CABP, of 85% to 90% are projected, with an anticipated dropout rate by Day 4 of at most 5%. However, since subjects who dropout from the study prior to Day 4 will be included in the denominator for the calculation of the proportion of subjects with favourable clinical response at Day 4, an attained favourable response rate at Day 4 of 81% to 86% is anticipated in each treatment group. Based on these attained favourable clinical response rates at Day 4, a non-inferiority margin of 12.5%, and using the Farrington-Manning sample size approach for the Miettinen and Nurminen method, it has been determined that approximately 414 adult subjects (207/arm) will need to be included in the MITT analyses set in order for the statistical test to have a-priori at least 90% power at the 1-sided 2.5% significance level when the attained favourable response rate is at least 81%. Given the number of subjects needed in the MITT (N=414) analyses set and assuming a TB rate of 15%, 488 subjects will need to be enrolled into the study.

[figure not shown]

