### 18.2 Secondary Efficacy Endpoints

The secondary analysis variables are listed below

- Clinical response at Day 4 (mMITT and CE analyses sets)
- Investigator determined Clinical outcome at EOT (MITT, mMITT and CE analyses sets)
- Investigator determined Clinical outcome at TOC (MITT, mMITT and CE analyses sets)
- Hospitalisation prior to FU (MITT analyses set)
- By-pathogen clinical response at Day 4 and by-pathogen clinical outcome at TOC (mMITT analyses sets)

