### Partial Date

Missing day - Impute the last day of the month unless month is same as month of first dose of study drug then impute last dose date.

Missing day and month – Impute 31st December unless year is the same as first dose date then impute last dose date.

Note: For the purpose of displaying related events, events with relationship marked as “Missing” relationship will be considered as “Treatment Related”.

In case the AE end date is missing, the AE will be kept as ‘ongoing’. The duration of AE in the listing will be displayed as >xx days. Here xx days means the total duration in days from the date when the AE started till the end of the study.

Missing times, severity and causality for AEs will be queried for a value. No imputations will be made for missing times. AEs with a missing time will be considered treatment emergent if the date is on or after the first dose of the study drug, AEs with missing severity will be considered severe and AEs with a missing relationship to the study drug will be considered related to the study drug.

- For the primary efficacy outcome at Day 4, subjects with missing data will be considered Indeterminate response. By definition, subjects with Indeterminate response will be included in the denominator for analyses in the MITT analyses set.
- Missing values for other efficacy outcomes will be handled in a similar manner as the primary efficacy outcome.
- For evaluations at the TOC Visit, subjects with Indeterminate response will be included in the denominator for analyses in the MITT analyses set and will be excluded from the CE analyses set at TOC.

[figure not shown]

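### The Day 4 and EOT analyses in the CE set use one CE set defined at TOC, so later events decide who counts at Day 4, and the handling of missing Day 4 responses in CE is not fixed

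*SAP*

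**What the plan says.** - **Objectives and endpoints.** SAP Section 5.2 makes Day 4 response and EOT outcome in the CE set secondary objectives. Section 18.2 repeats the first as "Clinical response at Day 4 (mMITT and CE analyses sets".
- **The CE set.** Section 12.7 defines one CE set, and a subject must meet every criterion. Three criteria name TOC: the TOC visit falls 11 to 21 days from randomisation unless the subject was already a clinical failure; "Do not have a clinical outcome of Indeterminate at the TOC Visit"; and there is no other significant violation that may confound efficacy assessment at TOC. No criterion asks for a Day 4 or EOT assessment.
- **Where it is used.** Table 2 in Section 19.3 has one CE column, headed CE (at TOC). It is marked for Day 4 response, EOT outcome and TOC outcome. No other CE set is defined.
- **Missing data.** Section 23 keeps Indeterminate Day 4 responses in the MITT denominator and then says: "Missing values for other efficacy outcomes will be handled in a similar manner as the primary efficacy outcome". It excludes Indeterminates from CE only for evaluations at TOC.
- **Failures.** Section 18.2 carries failures at EOT forward to TOC.

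**The concern.** A set meant to hold subjects with evaluable data at a visit should be settled by what is known up to that visit. Here membership for Day 4 is settled one to two and a half weeks later. Loss to follow-up after Day 4, or a late TOC visit, cannot change a Day 4 response already recorded, yet either removes it. In the other direction, a subject with no Day 4 response but a valid TOC visit meets the CE criteria, and the SAP does not clearly say how that subject is counted.

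The CE analysis is the only adherence-restricted look at Day 4 response, since both sensitivity analyses in Section 19.2 stay in MITT. If later exclusion is related to Day 4 response, the CE rates are distorted. If that relation also differs by arm, or the arms truly differ, the CE treatment difference is distorted too.

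**Working it through.** **1. The plan's own figure.** Section 9 assumes "a non-inferiority margin of 12.5%, and using the Farrington-Manning sample size approach for the Miettinen and Nurminen method", with "at least 90% power at the 1-sided 2.5% significance level when the attained favourable response rate is at least 81" per cent, and Section 6 has subjects "randomised in a 1:1 ratio to either of the following 2 treatment arms". With unpooled variance:

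n per arm = (1.960 + 1.282)² × 2 × 0.81 × 0.19 / 0.125² = 207.0, so 207 per arm and 414 in MITT; 414 / 0.85 = 487.1, so 488 enrolled.

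Both stated figures reproduce. (The restricted-variance Farrington-Manning form gives 211 per arm, with 89.4% power at 207; the difference does not bear on this point.) The figures rest on MITT alone. The SAP states no CE size, so no CE power can be computed.

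**2. Timing.** Day 21 − Day 4 = 17 days and Day 11 − Day 4 = 7 days. CE membership for Day 4 is thus decided 7 to 17 days afterwards, counting in study days.

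**3. Following the text for four subjects.**

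| Subject | Day 4 response | Later course | In CE, hence in Day 4 CE? |
|---|---|---|---|
| A | Recorded | Cure at EOT, lost before TOC | No: Indeterminate at TOC |
| B | Recorded | Not a failure, TOC visit after Day 21 | No: outside window |
| C | Recorded, unfavourable | Declared failure at EOT | Not removed by the window or Indeterminate criteria |
| D | Missing | Valid TOC visit and outcome | Yes; counting at Day 4 not stated |

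A and B also leave the EOT analysis. The failure safeguard acts on a declared clinical failure (Section 18.2), which is not the same as an unfavourable Day 4 symptom response (Section 18.1). A Day 4 non-responder never declared a failure is treated like A or B.

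**4. Subject D: upper bound.** Section 9 states that "favourable clinical response rates at Day 4, obtained from studies of subjects with CABP, of 85% to 90% are projected". It allows for up to 5% of subjects leaving before Day 4. Keeping 5% Indeterminates in the denominator gives 0.85 × 0.95 = 80.75% and 0.90 × 0.95 = 85.5%. Excluding them gives 85% and 90%. The gap is at most 4.25 to 4.5 points per arm. It would be smaller in CE, because most subjects who drop out before Day 4 also lack a TOC outcome and leave CE.

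**5. Subjects A and B: illustrations with assumed exclusion rates (none are in the SAP).**

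*Equal arms.* True Day 4 response is 85% in both arms, and 5% of responders are excluded later. With b the share of non-responders excluded:

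CE rate = 0.85 × 0.95 / [0.85 × 0.95 + 0.15 × (1 − b)]

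| b | CE Day 4 rate |
|---|---|
| 10% | 85.7% |
| 20% | 87.1% |
| 30% | 88.5% |
| 40% | 90.0% |

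If b is 30% in both arms, both rates rise and the difference stays 0. If b is 10% in one arm and 20%, 30% or 40% in the other, a spurious difference of 1.4, 2.8 or 4.3 points appears. It favours whichever arm loses more non-responders.

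*Unequal arms.* Day 4 rates are 81% and 71% favourable, with 5% Indeterminate in each arm who also leave CE. Of favourable subjects 95% are retained, and of unfavourable subjects a share k:

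CE rate = 0.95 × fav / [0.95 × fav + k × (0.95 − fav)]

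| k | Rates | Difference |
|---|---|---|
| 0.95 (no selection) | 85.3% vs 74.7% | 10.5 points |
| 0.7 | 88.7% vs 80.1% | 8.6 points |
| 0.5 | 91.7% vs 84.9% | 6.8 points |

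Selection narrows the gap by 1.9 points (k = 0.7) or 3.8 points (k = 0.5) relative to no selection. Starting from 207 per arm with 71% in the nafithromycin arm, the Miettinen-Nurminen lower limits are −16.4 points (k = 0.7) and −13.9 points (k = 0.5). Both still miss −12.5.

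**The case against.** The strongest reply is that the SAP protects failures. The window criterion exempts subjects already deemed failures, and EOT failures are carried forward, so a declared failure is not Indeterminate at TOC. This stands: it limits selective loss of non-responders and makes the retention rates of 50% to 70% above look severe. It does not help subjects A and B, or a non-responder never declared a failure.

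A reader might infer that stopping study drug on Day 5 also removes a subject, by taking the 80% criterion as 80% of the full seven-day course. The text does not support that as fact. Section 12.7 refers to intended doses and allows evaluable failures after 48 hours and successes after 72 hours, and Section 17 calculates compliance from first to last dose. What remains is that the term is not tied to a visit.

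A reader might also infer that missing Day 4 responses definitely count as non-responders in CE. Section 23 names only the MITT denominator, and its extension to other outcomes does not mention CE. A missed Day 4 assessment is a significant deviation in Table 1, but Section 12.7 removes only violations that may confound TOC. The position is unclear rather than stated.

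A third inference, that the design biases the result towards non-inferiority, is possible but not shown. The spurious difference can favour either arm, and the unequal-arm examples do not change the conclusion.

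Finally, the choice is open: the Table 2 column is labelled, and Section 13 tabulates exclusions from each set with reasons by treatment. That makes imbalance visible but does not restore the excluded Day 4 data. The CE criterion on non-study antibacterials also runs to TOC, but the present point does not depend on it.

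**Conclusion.** The point holds as a defect in the secondary CE analyses at Day 4 and EOT. On the plain text, valid Day 4 and EOT data are dropped because of later events, and the counting of Indeterminate Day 4 responses in CE is left to interpretation. The resulting bias in the CE Day 4 difference has unknown size and direction. The 1.4 to 4.3 points between equal arms, and the 1.9 to 3.8 points between unequal arms, rest entirely on assumed exclusion rates. The 4.25 to 4.5 points per arm for missing data is an upper bound.

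Non-inferiority is concluded from MITT alone (Sections 9 and 19.1), so the primary test and the 414/488 sample size do not change. The correction should be made because it is cheap and the affected analyses are stated secondary objectives.

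**What to change.** Replace the single CE set in Section 12.7 with three:

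- **CE-Day 4:** eligibility, compliance, violations and outcome availability judged up to Day 4; Indeterminate at Day 4 excluded.
- **CE-EOT:** the same, judged up to EOT; Indeterminate at EOT excluded.
- **CE-TOC:** the same, judged up to TOC, keeping the present TOC window and its exception for failures; Indeterminate at TOC excluded.

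State that intended doses means doses due up to the visit in question. In Section 23, say outright that Indeterminates at a visit are excluded from that visit's CE set. In Table 2, use the matching set in each row, and list the change in Section 26.

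The cost is SAP wording and two more population flags from data already collected. The one downside is that the three CE analyses no longer share a denominator, which footnotes to the tables can explain.
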